**Risks and Adverse Events Associated with Psilocybin**

Previous research using doses of 30 and 40 mg reported no serious adverse events (Griffiths et al., 2006, 2011; Bogenschutz et al., 2022).

Key risks of psilocybin, as noted in literature, include prolonged psychotic symptoms, flashback phenomena or Hallucinogen Persisting Perceptual Disorder (HPPD), and anxiety reactions. Studies at the John Hopkins Center for Psychedelic Research, encompassing over 300 participants and 600 dosing sessions with 25mg psilocybin, recorded no cases of HPPD. HPPD itself is rare, with a prevalence of 4-4.5% among lifetime users of hallucinogens, though the specific incidence related to psilocybin is unclear (Kurtom et al., 2019). Prolonged psychotic responses in clinical psilocybin studies are infrequent, less than 1% (Studerus et al., 2011).

Anxiety during psilocybin experiences is common (Griffiths et al., 2006; Carhart-Harris et al., 2016a). A survey involving 1993 participants (mean age 29) exploring challenging experiences with psilocybin found that 84% benefited, despite psychological distress. The severity of the experience positively correlated with long-term increases in well-being (Carbonaro et al., 2016).

This study includes robust preparatory and integration sessions to minimize distress and maximize therapeutic outcomes. Therapists will receive specialized training to handle challenging experiences in real time.

Although the MRI examinations, during which patients need to lie still for about 1 hour, might be perceived as uncomfortable by some, they pose no health risk for the patient if routine safety precautions are followed (i.e. careful screening for contraindications for undergoing MRI and ensuring that no ferromagnetic metal objects are brought near the scanner).

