4.3 Primary Endpoint

- **Safety:** Incidence of adverse events (AEs) and serious adverse events (SAEs) during the trial period.

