5.1 Overall Trial Design

- A Phase IIa, open-label, randomized controlled trial with two arms:

1. Active treatment arm; Two dosing sessions with psilocybin 25mg with psychological support alongside TAU.

2. Active comparator control arm; TAU only.

TAU includes specialized care offered in an eating disorder unit in Region Skåne, Sweden. If the active treatment arm is determined to be safe, tolerable, and preliminarily effective during the follow-up assessment, participants in the control group will have the option to switch to the active treatment while maintaining their usual specialized care.

This design minimizes ethical concerns regarding withholding a potentially effective treatment.

Participants will be randomly assigned (1:1) to either the intervention or control group.

Block randomization stratified by age group (16–17 and 18–35 years) will ensure balanced representation.

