**Rationale for dosing interval:**

Several clinical trials have consistently demonstrated that administering two doses of psilocybin spaced 2 to 4 weeks apart is both safe and therapeutically appropriate when delivered under professional supervision with structured integration support (Bogenschutz et al., 2022; Carhart-Harris et al., 2021; Davis et al., 2021; Garcia-Romeu et al., 2015; Gukasyan et al., 2022). These dosing intervals are grounded in empirical findings from multiple populations and indications. For instance, Carhart-Harris et al. (2021) administered two 25 mg doses of psilocybin three weeks apart to 59 individuals with depression, reporting no serious adverse events (SAEs) and only transient effects such as headache and nausea. Garcia-Romeu et al. (2015) conducted a feasibility study in 15 smokers, administering 20 mg/70 kg and 30 mg/70 kg doses spaced by approximately two weeks; again, no SAEs were reported, and the design highlighted psychological integration. Davis et al. (2021) employed a two-week interval between doses in 24 patients with depression. Finally, Bogenschutz et al. (2022) studied 93 individuals with alcohol use disorder, spacing two 25 mg doses four weeks apart, with no serious adverse drug reactions noted. Collectively, these studies support the 4 week interval as an evidence-based standard that balances therapeutic efficacy with participant safety.

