8.2 Methods for Measurement of Endpoints for Clinical Safety

Continuous clinical safety monitoring will be performed by licensed healthcare professionals at Lund University Hospital throughout the trial, from baseline to the final 12-month follow-up. The safety evaluations cover physical, biochemical, and psychological parameters relevant to psilocybin administration.

For a complete list and overview, please visit the Schedule of Assessments attached to the protocol.

- **Hepatic and renal function:** Blood samples will be collected to assess creatinine, albumin, PK-INR, ALAT, ASAT, GT, ALP, and bilirubin levels. These assessments will occur during screening, at baseline (Week 0), after each psilocybin dosing, at the primary endpoint, and at the 6-month follow-up (Week 24).
- **Glucose:**Measured at the same time points as above – during screening, baseline, after each dosing, at the primary endpoint, and the 6-month follow-up. Additionally, glucose levels will be assessed at 9- and 12-month follow-up visits.
- **Urine toxicology (U-tox):** Drug use screening will be performed at baseline, and again at 6-, 9-, and 12-month follow-ups.
- **Cardiovascular parameters (ECG, blood pressure, pulse):** These will be measured at screening, baseline, after each dosing session, during the first integration sessions (1 day post-dosing), and at all subsequent follow-ups.
- **Assessment of suicidality and psychiatric safety:** Suicidality will be assessed using the Columbia-Suicide Severity Rating Scale (C-SSRS) at baseline, after each psilocybin session, during integration, and at all follow-ups. Psychiatric symptoms will be monitored using the Brief Psychiatric Rating Scale – Extended (BPRS+).
- **Mental health symptoms:** Self-report instruments including the PHQ-9 (depression), GAD-7 (anxiety), and other measures will be completed at baseline, at each integration visit, at the primary endpoint, and at the 12-month follow-up.
- **Adverse Events (AE/SAE):** Spontaneously reported by participant patients or by clinician at all in-person visits from first dosing onwards, including all integration and follow-up assessments.

All data will be collected under Good Clinical Practice (GCP) conditions and entered the electronic case report form (eCRF) by trained personnel.

9. Handling of Adverse Events

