9.1 Definitions

- *Adverse Event (AE):* Any untoward medical occurrence in a subject to whom a medicinal product is administered and which does not necessarily have a causal relationship with this treatment.

*Adverse Reaction (AR):* In the pre-approval clinical experience with a new medicinal product or new use of a medicinal product, and particularly as the therapeutic dose(s) may not be established, all noxious and unintended reactions to the medicinal product related to any dose should be considered an adverse reaction (AR). The phrase “reaction” to a medicinal product means that the causal relationship between the medical product and an adverse event is at least a reasonable possibility, that is the relationship cannot be ruled out.

*Serious Adverse Event (SAE) Serious Adverse Event (SAE): Any untoward medical occurrence that at any dose requires inpatient hospitalization or prolongation of existing hospitalisation, results in persistent or significant disability or incapacity, results in a congenital anomaly or birth defect, is life-threatening, or results in death.*

*Medical and scientific assessment will be made to determine if an event is serious.*

*Suspected Unexpected Serious Adverse Reactions (SUSAR)*: An adverse reaction/event that is unexpected, serious, and suspected to be caused by the treatment, i.e. adverse reactions/events that are not included in the RSI section of the Investigator’s Brochure (IB) or SmPC.

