9.3 Reporting and Registration of Adverse Events

- AEs will be recorded by clinicians in the research team at each contact point with a study participant and reported in the REDCap documentation system and a manual standardized AE log template and serious events will be reported to the relevant authorities.

Serious adverse events (SAEs) will be reported within 24 hours of the investigator becoming aware, in accordance with Article 41 of CTR 536/2014.

- Suspected Unexpected Serious Adverse Reactions (SUSARs) will be reported to all investigators and Läkemedelsverket (LVM).

- All AEs and SAEs will be collected from Dosing 1 until final follow-up at 12 months.

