10.2 Statistical Analyses

This will be an open label, two-arm, active comparator (TAU; treatment as usual), , randomized controlled, between- and within-subjects, design in up to 40 completing patients meeting DSM-5 criteria for eating disorders. The patients will be randomly allocated to the psilocybin treatment-arm. The study analyses will enable comparison of efficacy between psilocybin-treatment and treatment as usual, as well as longitudinal within-patient efficacies.

- Primary Baseline Analyses:
  The primary analyses will involve descriptive statistics for demographic and baseline characteristics, ensuring comparability across groups, and control for follow-up measurements.
- Primary Endpoints analysis
- We will analyse differences in the number of participants and severity experiencing AE/SAE between the groups standardized forms for AE/SAE capturing: Event description, Start and end dates, Severity (e.g., mild, moderate, severe), Relatedness to intervention (assessed by safety review committee), Action taken.

The primary statistical methods will be:

- Descriptive Frequencies and Percentages.
- Comparing Proportions (Most Common for "Incidence") (Chi-squared test (or Fisher's Exact Test): Fisher's exact test is preferred for small cell counts (<5).
- Risk Ratio (RR) or Odds Ratio (OR) with Confidence Intervals: Report these measures of effect size to quantify the magnitude and precision of the difference between groups. An RR > 1 would indicate a higher risk in the intervention group.
- Comparing Severity and Relatedness is assessed with Mann-Whitney U test or Student t-test to compare severity distributions between groups.
- Secondary Endpoints:
  For secondary endpoints (e.g., changes in fMRI connectivity, BDNF, rating scales), group comparisons, including t-test, ANOVA, and Repeated Measures ANOVA will be utilized. When controlling for variables such as individual differences, ANCOVA or MANCOVA will be utilized. Principal component analysis (PCA) or independent component analysis (ICA) may be applied to identify patterns in fMRI data. Task-based fMRI data will be analysed using univariate models to investigate treatment effects in syndrome-related neural circuits (Celeghin et al., 2023; Bronleigh et al., 2022). Endpoints include longitudinal between- and within-person analyses.

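### The any-AE comparison pools expected dosing-day effects with later harm, so where acute AEs are frequent it mainly tracks those effects and the TAU background rate

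*Protocol*

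**What the plan says.** Section 4.3 defines the primary endpoint as "Incidence of adverse events (AEs) and serious adverse events (SAEs) during the trial period". It sets no limit by severity, duration or time since dosing. Section 10.2 gives the unit of analysis: "We will analyse differences in the number of participants and severity experiencing AE/SAE between the groups". It names chi-squared or Fisher's exact test and a risk ratio or odds ratio with confidence interval, and it reads a ratio above 1 as higher risk on psilocybin. Severity and relatedness are compared as well, and event dates are recorded, but no analysis in section 10.2 uses those dates.

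Section 9.3 sets the period: "All AEs and SAEs will be collected from Dosing 1 until final follow-up at 12 months". Section 8.2 describes ascertainment: "Spontaneously reported by participant patients or by clinician at all in-person visits from first dosing onwards". Section 9.1 defines an AE as "Any untoward medical occurrence in a subject to whom a medicinal product is administered", with no exception for expected drug effects.

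The psilocybin arm gets "Two dosing sessions with psilocybin 25mg with psychological support alongside TAU" (section 5.1). On acute effects, section 3 states "Anxiety during psilocybin experiences is common", and the dosing-interval rationale in section 5.1 reports from an earlier depression trial "only transient effects such as headache and nausea". Neither place gives a rate.

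**The concern.** A yes/no count per participant keeps only whether any event occurred. A psilocybin participant who is anxious or nauseous at the first session is a case from that day, and a later non-serious AE cannot change that status. TAU participants have no such exposure before any switch. The comparison therefore adds acute drug effects to later harm in one arm and sets the sum against the background rate in the other.

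If the TAU rate is low, the test can reject because of acute effects that the protocol already expects, with no lasting harm present. If the TAU rate is high, both arms approach 100% and added harm cannot show. In a trial whose primary objective is safety and tolerability, a reader could take a risk ratio above 1 as evidence of lasting harm, or a non-significant result as reassurance, and neither reading would be justified.

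The TAU rate is also weakly anchored. Collection starts at Dosing 1, which TAU does not have. The AE definition is tied to receiving a medicinal product. Section 7.4 lets TAU participants switch to psilocybin after month 6, inside the 12-month collection period.

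**Working it through.** There is no figure in the plan to reproduce: section 10.4 states that no power calculation was made, and no AE rate is given for either arm.

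**Inputs from the protocol.** 20 per arm (section 10.4); Fisher's exact test where cells are small (section 10.2); two-sided 0.05 (section 10.3; no multiplicity adjustment applied here); two dosing sessions (section 5.1).

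**Assumed inputs.** a = proportion with at least one acute AE over both sessions, 50% to 95%; b = TAU any-AE rate, 10% to 90%; L = proportion with a lasting AE caused by psilocybin, 0 or 30%. With independent sessions, a per-session rate of 50% gives a = 1 − 0.5² = 75%, and 70% gives 1 − 0.3² = 91%.

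**Model.** The psilocybin arm also receives TAU, so it carries the same background. Its total any-AE rate is 1 − (1 − a)(1 − b)(1 − L), taking the three sources as independent. Example: a = 0.90, b = 0.50, L = 0 gives 1 − 0.10 × 0.50 = 0.95; with L = 0.30 it gives 1 − 0.10 × 0.50 × 0.70 = 0.965.

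**Rejection probability, no lasting harm.** Full enumeration of both binomials; p < 0.05 with more cases on psilocybin.

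| Acute rate a | TAU 40% | 50% | 60% | 80% | 90% |
|---|---|---|---|---|---|
| 95% | 99% | 95% | 86% | 32% | 4% |
| 90% | 96% | 89% | 76% | 27% | 4% |
| 75% | 80% | 66% | 49% | 17% | 3% |
| 50% | 35% | 27% | 19% | 7% | 2% |

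At a TAU rate of 10% the figures are above 99% for a = 75% or more, and 84% for a = 50%.

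**Effect of adding L = 30%.** In the worked example, rejection moves from 89% to 93%. Over TAU rates from 5% to 95% in steps of 5 points, the largest increase is about 6 points at a = 90%, 13 points at a = 75%, and 28 points at a = 50% (27 points at TAU 40%: 35% to 62%).

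**Where the result turns.** If all 20 psilocybin participants are cases, 15 TAU cases give p = 0.047 and 16 give p = 0.106.

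**With acute events left out.** The psilocybin rate becomes 1 − (1 − b)(1 − L). With L = 0, rejection is about 1% at most. With L = 20%, it is 20% at TAU 10% (rates 28% v 10%) and 5% at TAU 50% (60% v 50%). The artefact goes, but power stays low.

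**SAEs alone.** 5 v 0 of 20 gives p = 0.047 and 4 v 0 gives p = 0.106. With 0 of 20, the one-sided 95% upper bound is 1 − 0.05^(1/20) = 13.9%.

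**The case against.** Five points can be made for the plan.

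First, a reader might infer that almost every psilocybin participant will be a case. The documents do not support that. Anxiety is called common and headache and nausea are named, without rates. At 50% acute the test does respond to lasting harm. This stands, and the size must remain conditional.

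Second, a reader might infer that the primary analysis carries no information on later harm. That is true only of the any-AE count. SAEs are named in the endpoint and are not swamped by mild dosing-day events, and a later, more severe event can alter the severity comparison. This stands in part. Severity does not separate a transient event from a lasting one, relatedness to psilocybin means nothing in TAU before a switch, and SAE comparisons at this size detect only large differences.

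Third, acute reactions belong to tolerability, so counting them is not an error, and nothing says that one test decides safety: section 10.1 focuses on the dosed cohort, section 9.5 provides committee review, and section 10.4 calls the study a pilot. This also stands. The fault is the pooling.

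Fourth, time windows are often left to a SAP, which is not shown. But the protocol itself fixes the endpoint, period, unit, tests and reading of the ratio, and these produce the problem.

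Fifth, section 5.2 labels Week 9 as the primary endpoint visit, so the comparison might stop there. That would reduce saturation in TAU, but both dosing sessions fall before Week 9, so the acute events would remain.

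**Conclusion.** The point holds in a limited form. The any-AE part of the primary analysis does not distinguish expected dosing-day effects from later harm. If about 75% or more of psilocybin participants have an acute AE, its result follows the TAU background rate: rejection falls from over 99% to 3–4% as that rate goes from 10% to 90%, while lasting harm in 30% moves it by at most about 13 points. At 50% acute, the TAU rate still moves the result more (84% to 2%), but lasting harm can move it by up to about 28 points, so the comparison is not blind.

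These sizes rest on assumed acute and TAU rates, independence of the three sources, 20 per arm and an unadjusted 0.05 level. The structural point needs only the protocol's own definitions and its own expectation of acute effects. SAEs and severity soften it without removing it. It should be corrected, but it does not invalidate the primary safety analysis as a whole.

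**What to change.** In sections 4.3 and 10.2, keep overall AE and SAE incidence and add a split by time since dosing:

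- (a) Acute: from each dosing day to its day-after visit, for both Dosing 1 and Dosing 2. Report this for the dosed cohort with exact confidence intervals, as the tolerability result.
- (b) Non-acute: all other time to Week 9. Both acute windows must be left out, because Dosing 2 at Week 4 falls inside this period.
- (c) Week 9 to month 6, or to the switch for TAU participants.

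Compare (b) and (c) between arms on matched calendar windows from a start date defined for both arms, counting participants with a new or persisting AE, so that an acute event that does not resolve is still counted. Report SAEs separately. Present (b) and (c) as differences with exact intervals instead of relying on a test, given the low power shown above. Draw the safety and tolerability conclusion from the acute, non-acute and SAE results together.

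The cost is analysis wording and extra tables: AE start and end dates are already captured under section 10.2. A common start date also means that section 9.3 must say when AE collection begins in TAU. The intervals will be wide.

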4.4 Secondary Endpoints

- Time to **Relapse:**

Defined as a composite outcome during the follow-up period, consisting of:

1. **≥7 % decrease in BMI** compared to post-hospitalization baseline BMI.

Rationale for 7 %: A 7% decrease in BMI reflects a significant deviation from expected weight gain in patients starting at a minimum BMI of 16, signaling potential relapse.

1. **Re-hospitalization for anorexia nervosa-related complications** (e.g., significant weight loss, medical instability). Data of hospitalization will be collected from hospital journal registers.
2. **Initiation of additional intensive psychiatric or nutritional interventions**, including day-patient or inpatient programs. Data of additional interventions will be collected from hospital journal registers.
3. **Self-reported significant deterioration in eating disorder symptoms** (e.g., severe food restriction, purging) as assessed by validated scales such as the Eating Disorder Examination Questionnaire 6.0 (EDE-Q 6.0).

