Currently, there are no approved pharmacological treatments for anorexia nervosa (Rahkonen et al., 2022). However, three pilot clinical trials have been approved and activated. NCT04052568 from John Hopkins is currently active. NCT04505189 from Imperial College is finished but not published. The third pilot study assessed the clinical tolerance and safety of 25mg psilocybin supported by psychological intervention in female AN patients with a BMI of 19 (Peck et al., 2023). The study found no significant changes in ECG, vital signs, or suicidality, and all adverse events (AEs) were mild and temporary. Two participants developed asymptomatic hypoglycemia post-treatment, which resolved within 24 hours with no other significant changes in laboratory values. Most participants reported subjectively meaningful experience, and a majority expressed that a second dose would have been beneficial. The study also observed significant reductions in eating disorder symptoms one-month post-treatment.

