**Rationale for Composite Outcome:**
This composite endpoint captures both clinical (BMI, hospitalization) and patient-centered (symptom deterioration) measures, aligning with the study’s aim to evaluate the efficacy of psilocybin in reducing the risk of relapse during a critical recovery period.

- Time to **Response:**

A clinically significant improvement in weight and psychological symptoms during the treatment period.

**Criteria**: **BMI Increase**: ≥10% increase in BMI from baseline (e.g., BMI 16 → BMI 17.6) or reaching a BMI ≥18.5 if achievable within the study period.

- Time to **Remission:**

The achievement and maintenance of weight restoration and psychological well-being, with no significant symptoms of anorexia nervosa.

**Criteria**: **Weight Restoration**: BMI ≥18.5 sustained for at least four weeks, or a weight within 90-95% of ideal body weight adjusted for age and height.

- Changes in AN symptom severity (measured by the Eating Disorder Examination from baseline to primary endpoint and follow-up 6 and 12 months.

- Changes in well-being from baseline to primary endpoint and follow-up 6 and 12 month.

- Changes in personality traits from baseline to primary endpoint and follow-up 6 and 12 months

- Changes in brain resting state connectivity (measured by fMRI), and commonly used task-based fMRI paradigms from baseline to primary endpoint. The task-based paradigms will involve food-related conditions, commonly used in the population (Celeghin et al., 2023; Bronleigh et al., 2022) as well as established paradigms involved in processing reward anticipation (Knutson et al., 2000; Ventorp et al 2022)

- Changes in peripheral BDNF measured in platelet-poor EDTA plasma from baseline to primary endpoint.

5. Trial Design and Procedures

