6.1 Inclusion Criteria

- Diagnosis of AN per DSM-5, including AN in partial remission.

- Have experienced at least one period of weight restoration to a minimum BMI of 17 followed by subsequent weight loss.

- Age 16-35.

- BMI >16

- Stable contact with a psychiatric unit.

- Ability to provide informed consent.

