6.2 Exclusion Criteria

- Psychosis, bipolar disorder, substance use disorder, family history of psychosis or bipolar disorder, refusal of birth control, lifetime psychedelic use.
- Cardiovascular conditions,
  - Resting systolic blood pressure >140 mmHg or diastolic blood pressure >90 mmHg at screening or baseline.
  - Clinically significant arrhythmias, tachycardia and QT prolongation.
  - History of stroke, myocardial infarction, or other significant cardiovascular events.
  - Seizure disorders or history of epilepsy.
- Diabetes mellitus, positive drug tests, suicidal intent, allergy or intolerance to drug content, blood or needle phobia.
- Metal pieces in the body (contraindicated by fMRI, assessed in each case by MR-technician)
  - Only for the MRI-part of the study
- Any other clinically significant medical condition that, in the investigator’s opinion, may pose a risk to the participant or interfere with study results.
- Care under the Swedish Compulsory Psychiatric Care Act (LPT).
- Ongoing treatment with medications that have clinically relevant 5-HT2A-receptor antagonistic properties and are therefore expected to directly block or substantially interfere with the pharmacodynamic effects of psilocybin. Such medications require an appropriate washout period prior to psilocybin administration, based on pharmacokinetic properties and clinical judgement. Medications without direct 5-HT2A-antagonistic effects are not excluded on this basis**.**
- Sustained weight restoration, defined as BMI > 21.0 for ≥ 6 consecutive months within the 12 months prior to screening, as documented in medical records.

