**All concomitant medications will be carefully documented and considered in the interpretation of clinical outcomes.**

The following psychiatric medications are prohibited in participants receiving psilocybin due to known or potential pharmacodynamic interactions and risk of attenuated psychedelic effects or adverse reactions:

•Monoamine oxidase inhibitors (MAOIs)

•Tricyclic antidepressants (TCAs)

•Benzodiazepines ≤ 2 mg lorazepam equivalents per day (must not be taken within 12 hours prior to psilocybin administration)

•Antipsychotics

•Lithium

Participants will undergo a thorough medication review during screening to identify potential pharmacological interactions. Medications with prohibited serotonergic activity require washout periods of 2–4 weeks before psilocybin dosing according to clinical practise guidelines.

- Participants who cannot safely discontinue contraindicated medications will not be included in the study.

- The washout will primarily be monitored by phone and a medical doctor within the research team appointed by the principal investigator, with in-person visits if needed. Participants who exceed the 8-week limit without dosing will be re-evaluated for eligibility by the principal investigator. The time from screening to first dosing shall not exceed 8 weeks regardless of washout status.

- Psychotherapy and other non-pharmacological treatments will be allowed throughout the study period as TAU if not deemed an exclusion criterion. Temporary daycare after discharge will be considered part of TAU rather than non-pharmacological treatment.

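### Patients who enter at BMI 18.5 or above can meet response and remission without any change, and the BMI reference for relapse is undefined

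*Protocol*

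**What the plan says.** All three time-to-event endpoints are defined in protocol section 4.4.

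- **Relapse** is "Defined as a composite outcome during the follow-up period, consisting of" four components. The BMI component is a fall of at least 7% "compared to post-hospitalization baseline BMI". The others are re-hospitalisation, the start of additional intensive care (day-patient programmes included) and self-reported symptom deterioration.
- **Response** is a BMI gain of at least 10% from baseline, "or reaching a BMI ≥18.5 if achievable within the study period".
- **Remission** is "BMI ≥18.5 sustained for at least four weeks, or a weight within 90-95% of ideal body weight", the latter adjusted for age and height.

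Eligibility sets the range of BMI at entry. Section 6.1 requires BMI above 16, accepts AN in partial remission, and asks for this history: "Have experienced at least one period of weight restoration to a minimum BMI of 17 followed by subsequent weight loss". It does not ask for a hospital stay. The only upper restriction is in section 6.2: "Sustained weight restoration, defined as BMI > 21.0 for ≥ 6 consecutive months within the 12 months prior to screening".

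Section 8.1 lists the BMI decrease for relapse as measured at baseline, 5 weeks and 6 months. Section 7.3 adds: "Temporary daycare after discharge will be considered part of TAU rather than non-pharmacological treatment".

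**The concern.** A time-to-event endpoint should start with every patient free of the event and should record something that happens afterwards. Here the 18.5 threshold lies inside the eligible BMI range and no starting point below it is required. Patients who enter at or above it have the same outcome in both arms whatever the treatment does. For those just below it, the hurdle depends on entry BMI. Randomisation is stratified by age group only (section 5.1), so with 20 per arm the groups can differ in entry BMI by chance.

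The relapse reference raises a different problem. A patient never hospitalised has no post-hospitalisation BMI. For others the term could mean a discharge weight from before the trial or the week-0 weight. The trial is open-label, so if the choice is made late it is made with allocation known.

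The results have a use. Time to relapse is the efficacy outcome named in section 4.2, and section 7.4 makes the control arm's offer of psilocybin depend partly on preliminary efficacy.

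**Working it through.** **Inputs.** Response: 10% gain or BMI 18.5. Remission: BMI 18.5 for four weeks, or 90–95% of ideal weight. Relapse: 7% fall (all section 4.4). Entry: BMI above 16, no upper limit except above 21.0 held for six months (sections 6.1, 6.2).

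**The plan's own figure.** The response example goes from 16 to 17.6. 16 × 1.10 = 17.6, so it reproduces.

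**Response.** The BMI needed is the smaller of 1.10 × entry BMI and 18.5. The two are equal at 18.5 / 1.10 = 16.82. Above that the fixed threshold is the easier route, and the gain needed is 18.5 / entry BMI − 1, or zero from 18.5 upwards.

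| Entry BMI | BMI needed | Gain needed |
|---|---|---|
| 16.5 | 18.15 | 10.0% |
| 17.0 | 18.5 | 8.8% |
| 17.5 | 18.5 | 5.7% |
| 18.0 | 18.5 | 2.8% |
| 18.5 or more | already met | 0% |

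**Remission, BMI route.** If the four weeks are counted from week 0, a patient entering at 18.5 or more who does not change completes them at week 4. The next listed BMI measurement is at 5 weeks (section 8.1) or week 9 (section 5.2).

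**Remission, ideal-weight route.** No duration is attached. The protocol does not say which BMI corresponds to ideal weight. Assuming 20 to 22, the 90–95% band runs from 18.0–19.0 (at 20) to 19.8–20.9 (at 22). Both lie inside the eligible range, so this route may be met at entry.

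**Relapse, BMI component, two readings.**
- *Week-0 reference.* The change on day 0 is 0%, so nobody starts in relapse.
- *Earlier discharge reference.* The component is already met when the discharge BMI is at least entry BMI / 0.93. That is 16 / 0.93 = 17.20 for entry just above 16, 17 / 0.93 = 18.28 for entry at 17, and 18.5 / 0.93 = 19.89 for entry at 18.5.

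**Conflict between endpoints on the week-0 reading.** A 7% loss still leaves BMI at 18.5 or more when entry BMI is at least 18.5 / 0.93 = 19.89. For example, 20.0 × 0.93 = 18.6. That patient has relapsed and still satisfies the response criterion.

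**Definition against criterion.** The introductory sentences for response and remission ask for psychological improvement or well-being as well as weight. The criteria listed under them are weight only.

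**Daycare.** Starting a day-patient programme counts towards relapse in section 4.4, while section 7.3 treats temporary daycare after discharge as part of TAU.

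**The case against.** A reader might infer that all three endpoints can be met on day 0. The documents do not support that. Relapse is confined to follow-up, and three of its four components are new events. Section 8.1, and the section 4.4 rationale for the 7% figure, which speaks of patients starting at the trial's minimum BMI, both point to study baseline as the reference. Nor does the weight history in section 6.1 put patients below a discharge weight: it need not refer to the last hospital stay, and the smallest fall it implies, from 17 to 16, is 1 − 16/17 = 5.9%, short of 7%. Remission's BMI route needs four weeks.

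The wording of the response rule can be read as implying a start below 18.5. Even so, the text does not say what happens to a patient who starts above it.

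Section 10.2 adjusts the logistic models for response and remission for baseline BMI, so a chance imbalance need not decide those results. Adjustment does not, however, turn a criterion already met at entry into a treatment outcome.

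Risk-set rules are often left to the SAP, which is not shown. The threshold and the undefined reference, though, belong to the protocol's own endpoint definitions.

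Two further points weaken. The daycare passages can be read together if only care beyond planned step-down counts as additional, but the protocol does not say so. The 95% upper edge of the ideal-weight band matters little, because a patient above it usually qualifies through BMI 18.5.

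Finally, section 5.1 states that power for group comparisons is limited and that the focus is on safety, feasibility and tolerability. That stands and limits the weight of the point.

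**Conclusion.** The point holds in this form. Response can be met on day 0, and remission's BMI route by week 4, with no change in any eligible patient entering at BMI 18.5 or above. Below that, the gain needed for response depends on entry BMI, from 10% at 16.8 or less down to 0%. The ideal-weight route may also be met at entry, on the assumption about ideal weight stated above. The relapse reference is undefined. Only on the discharge reading could patients start in relapse; on the study-baseline reading the fault is the overlap with response from entry BMI 19.9 upwards.

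The number of patients affected cannot be computed. If entry BMI were uniform from 16 to 19, 20 or 21, the share at 18.5 or more would be 0.5/3 = 17%, 1.5/4 = 38% or 2.5/5 = 50%, so the figure simply follows the assumption. Such entrants are plausible: section 2 describes the earlier AN pilot as involving "female AN patients with a BMI of 19", and section 5.1 says that prior AN work used similar inclusion criteria. That single value is not this trial's distribution.

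A reader might treat this as a fault that must be cured before the trial can be interpreted. The documents do not support that: these are secondary endpoints and the primary safety endpoint (section 4.3) is unaffected. The weight is moderate.

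**What to change.** Amend section 4.4 as follows.

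1. Name the week-0 trial BMI as the relapse reference for every patient, and reconcile this with section 8.1.
2. Let the 18.5 route to response and remission count only for patients below 18.5 at week 0. Leave those at or above it out of the risk set for that route.
3. Apply the same rule to the ideal-weight route: a patient already in or above the band at week 0 is not at risk for it.
4. Reconcile the weight-only criteria with the definitions that also ask for psychological improvement. Those definitions name no scale, so the sponsor must either state a measure and threshold or narrow the definitions to weight.
5. Reconcile the day-patient component of relapse with the statement on daycare in section 7.3.

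Steps 1 and 2 also remove the overlap between relapse and response. A patient below 18.5 at week 0 who loses 7% is below 18.5 × 0.93 = 17.2 and cannot satisfy the 18.5 route at that measurement.

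Items 1 and 2 need no new data, since BMI is already measured at baseline. The cost is fewer patients at risk for response and remission, although those removed carry no information on treatment through that route. Patients at 18.5 or more would have only the 10% route to response (19.0 × 1.10 = 20.9). Whether that is a meaningful target for them is an endpoint decision for the sponsor to state.
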